### Sample size

The main objective of this study is to assess if a Group x Time interaction effect exists for movement control of the spine, i.e., if movement control of the spine changes differently between groups over the course of the intervention. To the best of our knowledge, currently no studies have been performed in which spinal movement control, as defined in the current paper, is both trained and assessed before and after training, which complicates the estimation of an expected effect size. For the study outcome to be clinically meaningful we have set the goal to detect or reject an arbitrary effect size of 0.25 (24). In other words, if the effect size would be below 0.25, we would consider this result to be too small to be of interest. Differences in movement control of the spine in low back pain patients and healthy controls in terms of tracking error of a spinal movement controlled tracking task were reported by Willigenburg et al. (12). The tracking error in healthy controls was 0.332 degrees (SD 0.103) and in low back pain patients 0.422 degrees (SD 0.634), which is a large effect size (>0.8). No data about the expected effect of a sensor-based movement control intervention on these outcomes are available. However, a recent study from Matheve et al. demonstrated that low back pain patients can alter their movement behavior using a sensor-based intervention during a single session (14). Hence, we expect that low back pain patients will be able to perform equally well on movement control tasks by the end of the intervention as healthy controls without an intervention. If the static motor control group reaches 75% of the effect of the sensor-based movement control group, corresponding to an effect size of 0.25 (considering the effect of the intervention is equally large as the standard deviation of the effect), a total sample size of 54 (27 per group) would suffice to demonstrate a Group x Time interaction effect at a power of 95%. In case of a drop-out an additional patient will be recruited (with a maximum of 10 patients).

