### Data collection and outcome measures

Patients will be tested at two instances, once before (T0: week 1) and once after the intervention (T1: week 10). In addition, we will contact them by email at 6- and 12-months follow-up (T2: week 26 & T3: week 52). Per follow-up moment, patients receive a maximum of 2 emails and 1 letter, to enhance completion of the follow-up. Table 2 highlights the measures collected at each point in time. At the start of the intervention study, patients' characteristics will be recorded to enable comparison of baseline characteristics of both groups.

**Table 2 T2:** Overview of outcome measurements in this study.

	**Intervention**		**Follow-up**	
	**T0**	**T1**	**T2**	**T3**
**Patient characteristics** Age, height, weight, BMI, gender, duration of complaints	X			
**Questionnaires** RAND-36, FABQ, NRS, ODQ, RMDQ	X	X	X	X
**Movement control assessment** Tracking tasks, clinical spinal movement control tasks, repetitive motion tasks and gait trials	X	X		
**Therapy adherence** EARS		X		

T0: week 1; T1: week 10; T2: week 26; T3: week 52.

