#### Primary outcome

Our primary outcome measure is movement control of the spine. This will be quantified using three spinal movement controlled tracking tasks and a clinical movement control test battery. The movement controlled tracking tasks are based on the tracking task used in the study of Willigenburg (12). The tracking tasks used in this study consist of one flexion-extension, one lateral flexion and one rotation task, and will be performed at T0 and T1 with 3 Valedo Motion inertial measurement units (IMUs) attached at the right thigh, pelvis (at S1 level) and at the sternum level. During these tasks, patients will be instructed to move their spine in order to keep its real-time representation (on a laptop screen located in approximately one meter in front of them at eye level) within a moving target. Patients are in a seated position. The patient's pelvis will be fixated with a frame, which will be used to guarantee that the spinal angle is changed without any hip motion. Each trial will last 2 min and 40 s, with the first 40 s being for learning the task, and the following 2 min for the actual measurement. During the flexion/extension task, the vertical position of the target on the screen will vary between values that correspond to 20 degrees trunk flexion and 10 degrees trunk extension. During the lateral flexion and rotation task, the horizontal position of the target on the screen will vary between values that correspond to 10 degrees left and 10 degrees right lateral flexion or rotation. In each tracking task, the target will follow a multi-sine with a main frequency of 0.025 Hz (one cycle each 40 s). All these movement excursions are within the maximum range of the tracking task that was used by Willigenburg (12). Formula 1 and Table 3 describe the movement profile of the tracking target in each task, illustrated in Figure 3. The reliability or minimal detectable changes of this movement control measurement is unknown.

**Table 3 T3:** Used offset and ROM for each movement plane and characteristics of the multi-sine-wave.

Movement plane	**Off**set	**ROM**	Excursion
Sagittal (flexion)	5	30	−10/20
Frontal (lateral flexion)	0	20	−10/10
Transversal (rotation)	0	20	−10/10
Sine no.	***Ampl***itude (%)	***f***requency (Hz)	**φ**: Phase (rad)
‘Main' Sine #1	80	0.025	0.00
Sine #2	10	0.215	0.22
Sine #3	6	0.185	0.14
Sine #4	4	0.250	0.84

Bold text in the table corresponds to bold text in Formula 1. ROM: Range of Motion.

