### Statistical analysis

To evaluate if movement control of the spine changes differently between groups over the course of the treatment, repeated measures ANOVAs will be used to evaluate if a significant Group x Time interaction effect exists for the tracking error during each tracking task separately, the average tracking error of the tracking tasks and the total score of the clinical movement control test battery. The main effects of Group and Time will also be assessed using the same ANOVA. In addition to the total score of the clinical movement control test battery by Luomajoki et al. (19, 20) the performance on the individual tests that comprise the test battery will also be reported per group at T0 and T1.

Secondary study parameters will be assessed in the same manner as described above without correction for multiple testing, because these analyses are of an exploratory nature, and we want to limit the probability of type 2 errors. For the questionnaires that will be filled out on more than two occasions, we will perform *post-hoc* independent t-tests, with LSD correction, comparing results between groups at each point in time. Patient characteristics and all questionnaires filled out during the first testing day will be compared between groups using independent sample *t*-tests without correction for multiple testing to evaluate if differences existed at baseline. Statistical analyses in this study will not be adjusted for baseline differences between groups, as recommended by de Boer et al. (32). Independent of normality, parametric statistics will be used in this study and the alpha level will be set at 0.05 (33).

Data from patients who attended less than 10 sessions are not included in the statistical analysis. In addition, the data is also not included if patients have dropped out of the study before T1.

Missing data will be handled by using complete case analysis with all repeated measures ANOVAs between T0 and T1 and independent *t*-tests between T0, T1 and T2 and between To, T1, T2 and T3.

All statistical analyses will be performed using R version 4.1.1.

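### Ruling out baseline adjustment costs precision in the T0–T1 tests and lets part of any baseline gap into the questionnaire t-tests

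*Protocol article*

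**What the plan says.** The Statistical analysis section of the protocol article fixes four things that bear on this point.

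- **T0–T1 outcomes.** It says that "repeated measures ANOVAs will be used to evaluate if a significant Group x Time interaction effect exists for the tracking error during each tracking task", and applies the same test to the average tracking error and to the clinical test battery total. Secondary outcomes are handled the same way.
- **Questionnaires with more than two occasions.** In addition there are post-hoc "independent t-tests, with LSD correction, comparing results between groups at each point in time". These compare raw scores.
- **Baseline.** Patient characteristics and first-day questionnaires are compared by t-test "without correction for multiple testing to evaluate if differences existed at baseline".
- **Adjustment.** "Statistical analyses in this study will not be adjusted for baseline differences between groups", with a literature reference given in support.

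Table 2 (Data collection and outcome measures) shows all movement control measures and all questionnaires collected at T0, except the exercise adherence scale, which is marked at T1 only. The Primary outcome section says of the tracking tasks: "The reliability or minimal detectable changes of this movement control measurement is unknown".

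**The concern.** The T0 value of the outcome is usually the strongest predictor of its later value, and here it is already collected. The plan excludes it as a covariate in every analysis. Two things are at stake.

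First, precision. In a trial of 60, a change-score test discards information that ANCOVA would use. The loss is largest when the T0–T1 correlation is low, which cannot be excluded for a measure of unknown reliability. The same section says it wants to keep type 2 errors down in the secondary analyses, and this choice works against that aim.

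Second, the pain, disability and quality-of-life contrasts. A raw comparison after baseline carries over part of any gap present at T0. The Group x Time test on the same questionnaire is pushed the other way by the same gap. The plan gives no rule for reading the two together, and the baseline tests lead to no action.

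**Working it through.** **Inputs from the protocol article.** Two groups and two times for the movement control outcomes; "the alpha level will be set at 0.05"; from Sample size, "we have set the goal to detect or reject an arbitrary effect size of 0.25", 95% power and 54 in total (27 per group); from Design, 60 planned (30 per group). The T0–T1 correlation rho is not given. Equal SDs (σ) at T0 and T1 are assumed.

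**1. Reproduce the sample size.** For a Group x Time interaction with effect size f, N patients and m = 2 times, the noncentrality is λ = f²·N·m/(1−rho). With f = 0.25, N = 54 and rho = 0.5, λ = 0.0625 × 54 × 2 / 0.5 = 13.5. On 1 and 52 degrees of freedom this gives power 0.9501, so 54 reproduces exactly. At other correlations the total needed for 95% would be 106 (rho 0), 76 (rho 0.3) or 34 (rho 0.7). The protocol's figure therefore implies rho = 0.5. In this calculation f = 0.25 is a between-group difference in change of 1.0σ.

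**2. Precision.** With two times the Group x Time F test is the square of a t-test on change.

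- Variance of change: 2σ²(1−rho)
- Residual variance under ANCOVA: σ²(1−rho²) = σ²(1−rho)(1+rho)
- Ratio ANCOVA/change: (1+rho)/2, never above 1

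| rho | Ratio | Variance saved | Saved in simulation, 27 per arm | Power at 54: change | Power at 54: ANCOVA | n per arm for 95%: change → ANCOVA |
|---|---|---|---|---|---|---|
| 0.3 | 0.65 | 35% | 33% | 0.8616 | 0.9655 | 38 → 25 |
| 0.5 | 0.75 | 25% | 21% | 0.9501 | 0.9862 | 27 → 21 |
| 0.7 | 0.85 | 15% | 14% | 0.9965 | 0.9990 | 17 → 15 |

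The power columns use the 1.0σ difference from step 1. The simulated saving includes the cost of estimating the slope.

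**3. What a baseline gap does.** Suppose there is no treatment effect and the groups differ by g SD at T0. The expected later difference is rho × g in the raw t-test. In the change-score test it is rho × g − g = −(1−rho) × g. Under ANCOVA both shifts are removed, provided the gap is a chance one.

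| g (SD) | rho | Raw t-test | Change score |
|---|---|---|---|
| 0.25 | 0.3 | +0.075 | −0.175 |
| 0.25 | 0.5 | +0.125 | −0.125 |
| 0.25 | 0.7 | +0.175 | −0.075 |
| 0.5 | 0.3 | +0.15 | −0.35 |
| 0.5 | 0.5 | +0.25 | −0.25 |
| 0.5 | 0.7 | +0.35 | −0.15 |

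The two shifts always differ by exactly g: rho × g + (1−rho) × g = g. At T1 both analyses are planned. For T2 and T3 the missing-data sentence names only t-tests. There rho is the correlation of T0 with that time, also not stated.

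**4. How often a gap arises.** With 30 per arm, the SE of a standardised baseline difference is √(2/30) = 0.258. The chance of a gap of at least 0.25 SD is 2 × [1 − Φ(0.25/0.258)] = 0.333; for at least 0.5 SD it is 0.053. Both figures treat allocation as if random.

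**The case against.** The strongest reply is that the primary test is sound as planned. It uses T0, it removes the raw baseline difference, and on the inputs that reproduce 54 it already has 95% power. That stands. A reader might infer that the primary outcome ignores baseline, or is underpowered for want of adjustment; the documents support neither. If the Sample size wording is instead read as a difference of 0.25 SD of change, power at 27 per arm is about 15%, or 18% with ANCOVA at rho 0.5. That is a separate problem which adjustment does not cure.

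A reader might also take a 15% to 35% loss as a property of this trial. It is not: it assumes rho between 0.7 and 0.3, and the protocol gives no correlation.

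Nor does a baseline gap pass in full into the questionnaire results; it enters as rho × g. Those t-tests are labelled post-hoc, the secondary analyses are exploratory, and a comparison at T0 would make a gap visible. This limits the harm but does not tell the reader how to interpret a discrepancy.

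It is also tempting to say that ANCOVA must estimate the same effect because allocation follows start date. Allocation is quasi-random and non-concealed, in runs of five. Patients with fewer than 10 sessions or who drop out before T1 are then excluded. Equal expected baselines are plausible but not guaranteed. If groups differ systematically, the two methods can target different effects, and ANCOVA under-corrects when T0 is measured with error. This part of the objection stands and shapes the fix.

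Finally, the no-adjustment sentence follows the baseline tests and cites a reference, which could not be checked here. It may be meant to prevent covariates being chosen because a baseline test was significant. Declining that is right, but as worded the sentence also bans a prespecified T0 covariate, which is a different matter.

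**Conclusion.** The point holds in a limited form. For the T0–T1 outcomes the planned test is valid, and the loss is one of precision only: 25% of variance at the rho implied by the sample size (power 95.0% against 98.6% at 54), and 35% to 15% if rho lies between 0.3 and 0.7. These figures assume equal SDs at T0 and T1.

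The weightier part concerns the questionnaires. The unadjusted t-tests at T1, T2 and T3 move with a baseline gap by rho × g, and the change-score test moves the opposite way. A gap of at least 0.25 SD would arise by chance in about one trial in three. Averaged over truly random allocation neither test is biased; the problem is how to read the one trial that is run, with whatever gap it has. The change is worthwhile because it is almost free, not because the primary analysis fails without it.

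**What to change.** Replace the no-adjustment sentence with:

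> Each movement-control outcome now tested by Group x Time (each tracking task, the average tracking error and the clinical test battery total) is analysed by ANCOVA of T1 on group and the T0 value of the same outcome; questionnaire contrasts at T1, T2 and T3 are adjusted for the T0 score. No covariate is chosen on the basis of a baseline significance test.

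Keep the repeated measures ANOVA as a sensitivity analysis, since the two methods could estimate different effects if the analysed groups were not comparable in expectation. Describe baseline characteristics by group without significance tests. The wording keeps every tracking task and the battery in the analysis, so the set of primary outcomes is unchanged.

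The cost is one degree of freedom per model and reliance on comparable expected baselines. No extra patients, visits or measurements are needed.

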Movement control over less centrally located joints, such as the elbow or knee, can be trained using functional tasks, like bringing a spoon to the mouth or kicking a ball toward a pylon. The success of the execution (not spilling the soup or knocking over the pylon) can be used as an indication of good control over the movement of the joint. Providing meaningful feedback on spinal movements is more complicated. Sensors that measure spinal movements can offer a solution (14). There are several sensor-based training systems available on the market, but currently only a few randomized controlled trials incorporating these technologies have been published (15, 16). These sensor-based training systems can be used to offer accurate real-time feedback on spinal movements, which could help to improve spinal movement control. These systems provide the possibility to train spinal movement control relatively independent without the need of intensive supervision and/or a highly experienced therapist (17). Moreover, the training sessions are relatively easy to standardize and the progression from simple toward complex movements can easily be adapted to each patient's abilities and needs. The sensor-based exergames could be more engaging and motivating than conventional motor controlexercises, which might increase therapy adherence (18).

This paper describes the protocol for a randomized controlled trial to evaluate if a sensor-based movement control intervention enhances movement control of the spine in low back pain patients to a greater extent than a standard static motor control intervention. We will assess movement control using a custom made spinal movement controlled tracking task and a clinical test battery by Luomajoki et al. (19, 20). We hypothesize that a sensor-based movement control intervention will enhance movement control of the spine in low back pain patients measured by spinal movement controlled tracking tasks to a greater extent than a standard static motor control intervention. The majority of the tests in the clinical test battery by Luomajoki et al. (19, 20) involve no spinal movement, hence we hypothesize that the static motor control group will improve more on this outcome than the sensor-based movement control group.

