### Randomization, blinding and treatment allocation

This study is quasi-randomized and non-concealed. Patients will be screened in the first week of the multidisciplinary rehabilitation programme (2 weeks prior to baseline data collection). Enrolment and allocation will be 1 week prior to baseline data collection after consent of the patient. Patients will be enrolled and allocated to each intervention by one of the investigators ([name]) based on the starting date of the multidisciplinary rehabilitation programme. The research team has no influence on the starting date of each patient. If two patients start on the same date, allocation order will be alphabetically (based on the patients last name). The first five patients were allocated to the static motor control group, followed by five patients in the sensor-based movement control group and so forth until 30 patients have completed each intervention. This random allocation sequence was chosen by the investigators to keep group therapy planning feasible. Patients and therapists will not be blinded as this is practically impossible, however they will not be informed about the hypotheses of the study. The primary study outcome (spinal movement tracking error) will be calculated using a computer algorithm (custom made in D-flow, Motek, Amsterdam, The Netherlands) that will work independent of treatment allocation. Investigators involved in the statistical analysis will not be blinded to group. The clinical movement control battery tests will be recorded on video and scored by two examiners that are blinded to time (before/after intervention) and allocation.

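### The only analysis the protocol states is of patients with at least 10 sessions who stayed to T1, which leaves the group comparison open to selection bias of unknown size

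*Protocol article*

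**What the plan says.** Statistical analysis sets two exclusions. The first is "Data from patients who attended less than 10 sessions are not included in the statistical analysis". The second is that "the data is also not included if patients have dropped out of the study before T1". Neither is labelled as a per-protocol or sensitivity rule. For what remains, "Missing data will be handled by using complete case analysis with all repeated measures ANOVAs between T0 and T1".

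Recruitment is organised around the same patients. Randomization, blinding and treatment allocation fills the arms in runs of five "until 30 patients have completed each intervention", and Sample size allows up to 10 extra patients to be recruited in place of drop-outs. The term completed is not defined.

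Two other statements bear on the rule. The Introduction says that exergames could be more engaging than conventional exercises, "which might increase therapy adherence". The end of the Introduction and the Discussion both name therapy adherence as something to be compared between the interventions.

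**The concern.** Attendance and drop-out both occur after allocation, under treatments that patients and therapists know. If low attenders or leavers would have changed differently from those retained, and the arms lose them at different rates, the retained groups no longer differ by treatment alone. A difference can then be created or hidden. Recruiting further patients restores the count but not the comparison.

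The attendance rule does the avoidable damage. A patient who attended 9 sessions and was tested at both T0 and T1 has exactly the data that the repeated measures ANOVA needs, and is dropped anyway. The rule also cuts off the low end of the adherence comparison for patients who reach T1 with fewer than 10 sessions.

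**Working it through.** **1. What the threshold means.** Interventions gives two supervised sessions a week for 8 weeks: 2 × 8 = 16 (4 individual + 12 group). Attendance is registered for these sessions, so the threshold is read here as 10/16 = 62.5% of supervised sessions. Home exercise is not part of it.

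**2. Who is removed.**

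| Patient | T0 and T1 tests available? | Stated plan | All allocated, available data |
|---|---|---|---|
| 10 or more sessions, tested at T1 | yes | analysed | analysed |
| Fewer than 10 sessions, tested at T1 | yes | excluded | analysed |
| Left before T1 | no T1 | excluded | no T1 to analyse; reported by arm |

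The two approaches differ in the second row. For the T0–T1 ANOVA, complete case analysis would already omit the third.

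**3. The plan's own sample size.** Sample size gives 54 in total (27 per group), 95% power and effect size 0.25; alpha is 0.05. The within-between interaction has λ = f²·N·m/(1 − ρ) with 1 and N − 2 degrees of freedom. With f = 0.25, m = 2 and ρ = 0.5 (assumed; not stated), λ = 0.0625 × 54 × 2 / 0.5 = 13.5 and power is 0.950. So 54 reproduces when 0.25 is read as Cohen's f. In SD units of change, λ = n·d²/2 with n = 27 gives 13.5 = 13.5·d², so d = 1.0.

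**4. Bias from the exclusions.** Let p be the proportion excluded in an arm and D the mean change of retained minus excluded patients, in SD of change. The arm mean over everyone is (1 − p)·R + p·(R − D) = R − p·D, so the retained mean R is off by p·D. With the same D in both arms, the contrast is biased by (p₁ − p₂)·D. All rates and gaps below are assumptions.

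| Excluded | D = 0.5 | D = 1.0 |
|---|---|---|
| equal rates | 0 | 0 |
| 10% vs 20% | 0.10 × 0.5 = 0.05 SD | 0.10 × 1.0 = 0.10 SD |
| 5% vs 25% | 0.20 × 0.5 = 0.10 SD | 0.20 × 1.0 = 0.20 SD |

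**5. Effect on the test.** With 30 per arm, the standard error of the difference in change is √(2/30) = 0.258 SD. Under no true effect, the two-sided 5% test rejects with probability 1 − Φ(1.96 − b/0.258) + Φ(−1.96 − b/0.258):

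- b = 0.05: 5.4%
- b = 0.10: 6.7%
- b = 0.20: 12.1%

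**6. Expected yield (a separate, minor matter).** Study setting assumes 20% drop-out. The cap is 60 + 10 = 70 patients, and 70 × 0.8 = 56 completers. Sixty completers would need 60/0.8 = 75 enrolled; 54 would need 54/0.8 = 67.5, so 68. Under Binomial(70, 0.8), the chance of at least 60 completers is 0.147 and of at least 54 is 0.776, before any attendance exclusion. Power at 56, on the basis in step 3, is 0.957.

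**The case against.** The strongest reply is that harm is possible but not shown, and that several tempting extensions go further than the document.

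- **A reader might infer that exclusions are expected to differ by arm.** The Introduction says only that exergames might increase adherence, and nothing predicts unequal drop-out. With equal rates and gaps the bias is zero. This stands: the exposure is real, but its direction and size are unknown.
- **A reader might set 0.05–0.10 SD against the protocol's 0.25 and call it a large share.** The wording of Sample size (75% of an effect equal to its own SD) suggests 0.25 SD of change, of which 0.10 is 40%. The basis that reproduces 54 implies 1.0 SD, of which 0.10 is 10%. The protocol does not settle which is meant, so neither share should be quoted as its own benchmark.
- **A reader might infer that the trial will be too small.** It will not on expectation: 56 exceeds 54, and replacement offsets the losses. The shortfall is only against 30 completers per arm.
- **A reader might infer that the adherence comparison is lost.** Attendance is registered and can be reported for everyone allocated. Table 2 lists EARS at T1, so patients who leave earlier have no score under any analysis set. Truncation by the rule is limited to those who reach T1 with fewer than 10 sessions; how many is unknown.
- **A minimum-exposure set suits an efficacy question.** The Discussion uses that term, and such a set is defensible as a supporting analysis.
- **A separate analysis plan may define further sets.** It may, so their absence is not the point. The point is a rule that the protocol itself fixes without qualification.
- **Allocation is non-concealed and by start date.** Analysing all allocated patients does not cure that. It avoids adding a second source of selection.

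**Conclusion.** The concern holds in a limited form. The only analysis the protocol states conditions on attendance and retention after allocation, discards low attenders with valid T0 and T1 tests, and partly truncates the adherence comparison. The comparison is therefore open to selection bias.

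The amount cannot be known from the document. Under an assumed 10% versus 20% exclusion and a common gap of 0.5 to 1.0 SD, the bias is 0.05 to 0.10 SD and the false-positive rate about 5.4% to 6.7%. More unequal exclusion gives more, and equal rates with equal gaps give none. The stated total of 54 is not undermined by this point.

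The replacement cap is a minor mismatch: 20% drop-out and a cap of 70 are compatible on expectation with the 54 required, but not with 30 completers per arm.

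**What to change.** - Make the primary analysis all allocated patients with available data, in their allocated group, whatever number of sessions they attended.
- Invite every patient to the T1 test, whatever their attendance.
- Keep the set with 10 or more sessions as a labelled sensitivity analysis.
- Compare registered attendance in all allocated patients, and EARS in all who complete it.
- Report exclusions, drop-outs and reasons by arm.
- Count later recruits as additional patients, not as substitutes for those who left.
- Restate the expected yield: about 56 completers from 70, or about 75 enrolled if 30 completers per arm is the target.

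A mixed model on T0 and T1 may be used, but with two time points it adds little for patients without T1 and does not cure informative drop-out.

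The cost is plan wording and some additional T1 tests. The downside is that the estimate may be diluted compared with the completer analysis, which remains available as the sensitivity result.

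### The 6- and 12-month questionnaires are analysed by complete cases and separate t-tests under an LSD label that corrects nothing; a mixed model on all available scores would be better

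*Protocol article*

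**What the plan says.** All the rules are in the Statistical analysis section of the protocol article.

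- **Missing data.** "Missing data will be handled by using complete case analysis with all repeated measures ANOVAs between T0 and T1 and independent" t-tests. The sentence then names two groups of waves for those t-tests: T0, T1 and T2, and all four waves.
- **Follow-up tests.** Questionnaires completed on more than two occasions get post hoc "independent t-tests, with LSD correction, comparing results between groups at each point in time".
- **Multiplicity.** Earlier in the same paragraph, secondary parameters are to be assessed "without correction for multiple testing, because these analyses are of an exploratory nature". The general rule is that "parametric statistics will be used in this study and the alpha level will be set at 0.05".
- **Exclusions.** "Data from patients who attended less than 10 sessions are not included in the statistical analysis", and "the data is also not included if patients have dropped out of the study before T1".

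Under Data collection and outcome measures, the 6- and 12-month forms are requested by email, and at each follow-up moment "patients receive a maximum of 2 emails and 1 letter". The article gives no expected response rate at T2 or T3. The Study setting section gives only a general drop-out rate of 20%.

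**The concern.** There are three faults, all in the handling of secondary questionnaire outcomes.

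1. **Earlier scores are not used.** A patient who answers at T0 and T1 but not at T3 adds nothing to a T3 t-test, although the earlier scores predict the missing one. If the two groups of waves define the complete-case sets, a patient who returns T3 but missed T2 is also left out at T3.
2. **The LSD label is empty.** Least significant difference testing leaves each comparison at the nominal level. Its only protection is a significant omnibus test beforehand. The article states no such gate for T2 or T3, and the missing-data sentence ties the repeated measures ANOVAs to T0 and T1. The label also conflicts with the declaration of no correction in the same paragraph.
3. **The missing-data sentence is ambiguous.** It speaks of independent t-tests between time points, whereas the sentence on follow-up tests defines them as between groups at each time point.

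The Discussion acknowledges that pain and disability are what most patients care about. These are the outcomes followed to 12 months, so how non-response is handled affects how far those results can be trusted.

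**Working it through.** **The plan's own figure.** The article computes nothing for the follow-up analysis. Its one computed figure is 54 patients at 95% power for the T0–T1 interaction. Taking 0.25 as Cohen's f, with two groups, two measurements and an assumed within-patient correlation of 0.5, λ = f²·N·m/(1−ρ) = 0.0625 × 54 × 2 / 0.5 = 13.5. On F(1, 52) at 0.05 the power is 0.9501. The figure reproduces and is not touched by this point.

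**Forms lost under the literal reading.** Input from the article: 60 patients (30 per arm). Assumptions: all 60 have T0 and T1, and the response proportion r is the same at T2 and T3. If response is independent across waves, T3 forms returned = 60r, patients with all four waves = 60r², and returned T3 forms unused = 60r(1−r).

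| r | T3 forms returned | All four waves | Returned T3 forms unused |
|---|---|---|---|
| 0.9 | 54 | 48.6 | 5.4 |
| 0.8 | 48 | 38.4 | 9.6 |
| 0.7 | 42 | 29.4 | 12.6 |
| 0.6 | 36 | 21.6 | 14.4 |

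If exactly the same patients miss T2 and T3, the last column is 0 in every row. If the sentence means available cases at each time point, it is also 0.

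**Bias and precision at T3.** Simulation, 2,000 replicates: 30 per arm, four normal scores with SD 1, correlation 0.6 between any two waves, true group difference 0. The chance of a T3 response is 1/(1 + exp(−(1 − b·z))), where z is the T1 score and b may differ by arm. Complete case takes the difference in responders' T3 means. The alternative regresses T3 on T0 and T1 among responders within each arm and averages the predictions over all 30, which uses the non-responders' earlier scores as a likelihood-based model does. Entries are mean estimate (standard error) in SD units.

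| b, arm A / arm B | Response A / B | Complete case | Using T0 and T1 of all |
|---|---|---|---|
| 0 / 0 | 0.73 / 0.73 | −0.002 (0.309) | 0.000 (0.290) |
| 1 / 1 | 0.70 / 0.70 | 0.006 (0.296) | 0.002 (0.295) |
| 0 / 1 | 0.73 / 0.69 | −0.142 (0.305) | 0.014 (0.295) |
| −0.5 / 1 | 0.72 / 0.70 | −0.234 (0.302) | 0.000 (0.297) |

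Simulation error is about 0.30/√2000 = 0.007. When response depends on T1 differently by arm, complete-case bias is 0.14 to 0.23 SD, that is 0.142/0.305 = 0.47 to 0.234/0.302 = 0.77 of a standard error. With equal or no dependence it is nil. The precision gain is at most 1 − 0.290/0.309 = 6% of the standard error here.

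**What LSD leaves.** For k tests at 0.05 with no gate, the chance of at least one false positive is 1 − 0.95^k if independent. With 30 per arm and correlated waves, simulation (40,000 replicates) gives, per questionnaire score:

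| Time points tested | Independent | Correlation 0.3 | 0.5 | 0.7 |
|---|---|---|---|---|
| T2, T3 | 0.0975 | 0.095 | 0.090 | 0.085 |
| T1, T2, T3 | 0.1426 | 0.136 | 0.124 | 0.112 |
| T0 to T3 | 0.1855 | 0.173 | 0.155 | 0.133 |

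Counting ODI, RMDQ, three pain ratings, one FABQ total (an assumption; its scoring is not stated) and four RAND-36 scales gives 1 + 1 + 3 + 1 + 4 = 10 scores, so 10 × 2 = 20 tests at T2 and T3.

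**The case against.** The strongest reply is that these outcomes are secondary, that lack of correction is openly declared, and that the Discussion warns of low power for pain and disability. That stands. A reader might infer that the article passes off follow-up p-values as corrected; the no-correction statement in the same paragraph does not support this. The fault is one contradictory label. The term post hoc may hint at an earlier omnibus test, but no rule makes the t-tests depend on one.

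A reader might also infer that the 6- and 12-month comparisons will be biased. The documents do not show that. Bias in the group contrast needs response to relate to scores differently in the two arms, and nothing in the article documents this. It is only plausible: patients know their arm, and the Introduction expects the exergames to be more engaging. The reminders are described as a means to raise completion and are not evidence of poor response.

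Two further readings go too far. A T3 set that shrinks from 60 to 48 because 12 patients did not answer discards no T3 form, since those forms do not exist under any method. And the missing-data sentence cannot both define complete-case sets and prescribe tests that treat one patient's repeated scores as independent samples. Given the between-group definition of the tests, the second reading is strained, so the sentence needs clarifying and is not proof of a wrong test.

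Finally, entering T0 as a covariate would go against the article's stated decision not to adjust for baseline differences. That is correct, and the fix below does not depend on it.

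**Conclusion.** The point holds, within limits. For the T2 and T3 questionnaires the article fixes a method that ignores what non-responders reported earlier and, on its literal wording, may drop returned T3 forms: about 10 of 48 at an assumed independent 80% response, none if the same patients miss both waves or if available cases are meant. Bias in the group contrast was 0.14 to 0.23 SD under assumed arm-dependent non-response of about 30%, and negligible under equal dependence. The precision gain from a better model is modest. The LSD label gives no protection and contradicts its own paragraph; with three post-baseline tests per score, the chance of a false positive is 0.112 to 0.136 at correlations of 0.7 to 0.3.

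These sizes rest on assumed response rates, correlations and mechanisms, because the article gives none. Only secondary, exploratory outcomes are affected. The T0–T1 primary analysis and the sample size of 54 are unchanged. The change is worth making because it costs almost nothing.

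**What to change.** - For each questionnaire score, fit one likelihood-based linear mixed model to all available T0–T3 scores, with group, time, group × time and an unstructured covariance. Put T0 in the outcome vector, which respects the no-adjustment policy; use it as a covariate only if that sentence is revised.
- Report group contrasts with 95% confidence intervals at T1, T2 and T3. State that the model relies on data missing at random, and keep the complete-case t-tests as a sensitivity analysis.
- Delete the LSD label, so that the existing statement of uncorrected, exploratory testing stands alone.
- Reword the missing-data sentence so that it says which patients enter each time point and cannot be read as independent t-tests between time points.

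The cost is some wording and a little more R code, with no new data, plus reliance on the missing-at-random assumption. The model does not by itself restore patients removed for attending fewer than 10 sessions or dropping out before T1; that rule stays as written.
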